### Recruitment

A total of 50 participants diagnosed with MCI will be recruited from KHUGD and KHUMC. The participants will be recruited through advertising posters displayed in the hospitals and published in local newspapers, and banner advertisements in the subway, from June 2018.

### Randomization, allocation concealment, and blinding

Subjects will be randomly assigned to either the acupuncture or sham acupuncture group. Stratified block randomization will be used to control the influence of age and sex. An independent statistician who is not related to the intervention practice and outcome assessment will generate a random sequence using SAS® Version 9.4 (SAS Institute, Inc., Cary, NC, USA). This study will be conducted using a central randomized competitive recruitment method. Participants signing the informed consent form voluntarily and meeting the inclusion criteria will be eligible for randomization. An investigator will then assign the participants to groups based on the random sequence prepared and sent by an independent statistician via e-mail.

In this clinical trial, participants and assessors will be blinded to treatment allocation to decrease the risk of bias from the assigned acupuncture treatment group. However, practitioners will not be blinded. The participants will be informed that they will be treated either by real or sham acupuncture before they sign the informed consent form. The validity of the participants’ blinding will be assessed by an investigator who is not involved in either the patients’ allocation procedure or performance of the acupuncture treatment. The assessor will be blinded to the treatment group and prevented from speaking with the participants. Unblinding should be determined on a case-by-case basis and considered only in a critical medical emergency.

### Interventions

Acupuncture will be performed by specialists in Korean medicine following the details of the Standards for Reporting Interventions in Clinical Trials for Acupuncture (STRICTA) 2010 checklist (Table 1) [30]. Patients in both the acupuncture and sham acupuncture groups will receive 24 acupuncture treatments over 12 weeks at nine acupoints (GV20, EX-HN1, bilateral LI4, and ST36). In the sham acupuncture group, the acupuncture needle (a Streitberger needle) will not penetrate the skin. Streitberger needles are widely used as placebo needles in clinical trials [31–33]. During this trial, any other treatment for the improvement of cognitive function will be restricted in both acupuncture and sham acupuncture groups.

**Table 1 Tab1:** Details of acupuncture intervention

Item	Detail	Description
Acupuncture rationale	(1a) Style of acupuncture	Korean body acupuncture
	(1b) Reasoning for treatment	We selected the optimal treatment regimen based on university textbooks about the meridian and acupuncture, and a literature review of clinical trials investigating acupuncture therapy for mild cognitive impairment and dementia
	(1c) Extent to which treatment varies	None
Details of needling	(2a) Number of needle insertions per subject per session	9
	(2b) Names of points used (unilateral/bilateral)	GV20, EX-HN1, LI4 (bilateral), ST36 (bilateral)
	(2c) Depth of insertion	5–10 mm
	(2d) Response sought	None
	(2e) Needle stimulation	Manual
	(2f) Needle retention time	15 min
	(2 g) Needle type	0.30 × 30 mm, sterilized stainless steel needle (Asia-med GmbH & Co. KG, Germany)
Treatment regimen	(3a) Number of treatment sessions	24 sessions
	(3b) Frequency and duration of treatment sessions	2 sessions/week for 12 weeks
Other components of treatment	(4a) Details of other interventions administered to the acupuncture group	None
	(4b) Setting and context of treatment	Hospital outpatient department
Practitioner background	(5) Description of participating acupuncturists	Specialist in oriental neuropsychiatry or longer than 1-year career resident under the guidance of an oriental psychiatric specialist
Control or comparator interventions	(6a) Rationale for the control or comparator in the context of the research question	As placebo control, non-penetrating sham acupuncture needles will be used
	(6b) Precise description of the control or comparator	Non-penetrating acupuncture treatment at the same acupoints using a Streitberger device

### MRI scanning procedure

In order to evaluate neural correlates involved in improving cognitive functions following acupuncture treatment, brain imaging data will be acquired at baseline and over a 12-week period following acupuncture treatment. Imaging data will be acquired using a 3.0-T Philips Ingenia MRI scanner (Phillips Medical System, The Netherlands) at KHUGD and a 3.0-T Philips Achieva MRI scanner (Phillips Medical System) at KHUMC, both of which are equipped with a 32-channel head coil. We will use the same imaging parameters for both MRI scanners at the two sites. First, structural MRI will be recorded for standard space co-registration, and T1-weighted 3D turbo field echo sequences (repetition time (TR)/echo time (TE) = 9.9/4.6 ms, flip angle = 8°, voxel size = 1 mm isotropic) will be applied. A whole-brain T2*-weighted gradient echo blood oxygenation level-dependent (BOLD) pulse sequence (TR/TE = 2000/35 ms, flip angle = 90°, 34 axial slices, voxel size = 1.72 × 1.72 × 4.2 mm) will be used to obtain functional MRI (fMRI) data. We will use a task fMRI approach to investigate changes in brain responses to a cognitive task following acupuncture treatment. An adaptation of the WM task by Iordan et al. [34] will be used with emotional distractors. The emotional distractors are pictures depicting emotional scenes with high arousal and negative valence from the International Affective Picture System (IAPS; mean arousal and valence scales are 6.4 and 1.8, respectively) (Fig. 3). The task fMRI run will last for 8 min and 30 s for 12 tasks. The tasks will be presented visually using MRI-compatible video goggles (NordicNeuroLab, Norway). Participants will use a push-button to perform a WM task, and WM performance will be measured by the accuracy rate and response time. Two 8-min resting-state fMRI runs will also be acquired before and after the task fMRI run. Finally, diffusion-weighted images will be obtained using a spin-echo pulse sequence (TR/TE = 9125/97 ms, voxel size = 0.96 × 0.96 × 2.2 mm, 68 slices, b-value = 1000 s/mm^2^, 32 non-collinear directions).

**Fig. 3 Fig3:**

Paradigm of working memory task for a task functional magnetic resonance imaging (fMRI) run

### Outcome measurement

#### Primary outcome

The primary outcome is change in the Digit Span Test (DST) score from baseline to the end of treatment. The DST is used to measure WM, attention, and concentration, and is included in the Wechsler Intelligence Scale [35, 36]. Participants will hear sets of numbers and be asked to recall the numbers forwards or backwards. The digit sequences will be progressively longer until participants cannot recall the sets of numbers twice for a particular sequence length. The DST score is calculated by summation of the maximum number of digits successfully recalled forwards and backwards. The DST will be conducted at baseline, 4 weeks, 8 weeks, and within 2 weeks of the end of treatment.

#### Secondary outcomes

The Digit Symbol Substitution Test (DSST) is used to measure attention and psychomotor speed, and is sensitive to cognitive changes at high levels of cognition [37]. Digit–symbol pairs (e.g., 1/−, 2/┴ ... 7/Λ, 8/X, 9/=) and a list of digits will be presented to the participants. During a 90-s period, the participants draw as many paired symbols as possible under each corresponding digit. The DSST score is the number of correct symbols within a given time. The DSST will be assessed at baseline, 4 weeks, 8 weeks, and within 2 weeks of the end of treatment.

The MoCA is a widely used screening tool for MCI. Its cutoff score was 26 in the original version [38], but currently a cutoff score of 23 is suggested for better diagnostic accuracy [39, 40]. It consists of the trail-making test-B, three-dimensional cube copy, clock drawing test (CDT), confrontation naming task, short-term memory recall task, DST, serial 7 s, repetition of sentences, semantic verbal fluency task, and verbal abstraction task. In addition, orientation to time and place is also evaluated. The Korean version of the MoCA has been validated in the clinical setting and a cutoff score of 23 has been adopted [41]. The MoCA-K will be assessed at screening and within 2 weeks of the end of treatment.

The SNSB-II is a standardized neuropsychological test battery that has been validated in Korea [42–44]. This test is useful in distinguishing MCI from subjective memory impairment or dementia. It contains various cognitive assessment tools and dementia screening and evaluation tests, such as the Korean Mini Mental State Examination (K-MMSE), Short Version of the Geriatric Depression Scale (SGDS), Korean Barthel Activities of Daily Living (K-ADL), Korean Instrumental Activities of Daily Living (K-IADL), CDR, and GDS. The SNSB-II assesses five cognitive domains: attention, language and related functions, visuospatial function, memory, and frontal/executive functions. The attention domain includes the DST. The domain of language and related functions includes partial items of the Paradise Korean Western Aphasia Battery (K-WAB), Korean Boston Naming Test (K-BNT), calculation, and praxis test. The visuospatial function domain includes drawing and Rey Complex Figure Test (RCFT) copy. The memory domain includes the RCFT immediate and delayed recalls and recognition test and Seoul Verbal Learning Test (SVLT). The frontal/executive function domain includes the Korean Color Word Stroop Test (K-CWST), contrasting program and Go-No-Go test, Fist-Edge-Palm and alternating hand movement test, and Luria loop test. The SNSB-II will be assessed at screening and within 3 weeks of the end of treatment.

The Beck Depression Inventory-II (BDI-II) is a self-reported questionnaire to evaluate the severity of depression [45–47]. It consists of 21 symptoms related to the diagnostic criteria of major depressive disorder (MDD) in DSM-IV. Each symptom is graded on a 4-point Likert scale (0–3) and the total score ranges from 0 to 63. Higher scores mean higher levels of depression. The Korean version has been validated in healthy university students [48] and patients with depression [49, 50]. The BDI-II will be assessed at baseline and within 2 weeks of the end of treatment.

The State-Trait Anxiety Inventory (STAI) is also a self-reported scale to measure two types of anxiety: state anxiety and trait anxiety [51]. It consists of 40 questions, with each question rated on a 4-point Likert scale (1–4). The state and trait anxiety scores range each from 20 to 80. Higher scores mean higher levels of anxiety. The Korean version of Form Y of the STAI has been validated in high school and university students [52]. The STAI will be assessed at baseline and within 2 weeks of the end of treatment.

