**Methods:**

This study is a randomized, assessor-blinded, sham-controlled trial. Fifty participants with MCI will be randomly assigned to the acupuncture group (*n* = 25) or sham acupuncture group (n = 25). The acupuncture group will receive acupuncture treatment at nine acupuncture points (GV20, EX-HN1, bilateral LI4, and ST36) twice a week for 12 weeks. The sham acupuncture group will receive sham acupuncture treatment at the same points with non-penetrating sham needles. Both groups will be restricted from all other treatments for the improvement of cognitive function. The primary outcome measure is the Digit Span Test (DST). The secondary outcome measures are the Digit Symbol Substitution Test (DSST), Korean version of Montreal Cognitive Assessment (MoCA-K), Seoul Neuropsychological Screening Battery-II (SNSB-II), Beck Depression Inventory-II (BDI-II), State-Trait Anxiety Inventory (STAI), working memory (WM) task performance score, and structural/functional brain changes. Outcomes will be assessed at screening, baseline, 4 and 8 weeks, and after the end of treatment. We will also observe adverse events. In the statistical analysis, a full analysis set and per-protocol analysis will be performed.

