### Participants

#### Assessment of eligibility

Eligibility for this clinical trial will be assessed in two steps. First, a Korean version of the Montreal Cognitive Assessment (MoCA-K), Clinical Dementia Rating (CDR), and Global Deterioration Scale (GDS) will be evaluated. In eligible participants, we will then assess cognitive function using the Seoul Neuropsychological Screening Battery-II (SNSB-II), on a separate day.

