### Statistical analysis

In this study, statistical analyses will be performed by an independent statistician using full analysis set (FAS) and per-protocol (PP) analyses. The FAS refers to a set that is almost identical to the intention-to-treat (ITT) ideal of including all randomized subjects, but may exclude subjects who never received the treatment or missed baseline measurement after randomization. In addition, we will perform supplementary analysis of the PP analysis group. The PP analysis group refers to a set of subjects who completed the treatment originally allocated. Compliance in this study is deemed to be satisfied only by those who have undergone more than 70% of the total number of acupuncture treatments. In other words, out of the 24 treatments, participants who do not receive treatment more than 17 times are excluded from the PP analysis group because of violation of the protocol.

All demographic and baseline characteristics of participants will be presented based on descriptive analyses. Continuous data will be presented as the average and SD and analyzed using the independent two-sample *t* test or Wilcoxon rank sum test. Dichotomous data will be presented as frequency and percentile and analyzed using the chi-square test or Fisher’s exact test.

Post-test scores will be analyzed using analysis of covariance (ANCOVA), using each group as the fixed factor and baseline score with strata factors (such as sex and age) as the covariate. Within a group, the difference pre-treatment and post-treatment will be compared using the paired *t* test or Wilcoxon singed rank test for continuous data and the chi-square test or Fisher’s exact test for dichotomous data. For repeated measures outcomes, repeated measures analysis of variance (ANOVA) will be performed to compare differences between the times of measurement.

Statistical analyses of clinical outcomes will be performed using SAS® Version 9.4 (SAS Institute, Inc.). All tests will be two-sided and a *p* value <0.05 will be considered statistically significant. We will use multiple imputations for missing data.

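### A second pre-treatment DST score is already scheduled at screening; adding it as a separate covariate to the primary ANCOVA is a cheap gain in precision

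*Protocol article*

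**What the plan says.** All references are to the protocol article.

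- **Primary outcome.** "The primary outcome is change in the Digit Span Test (DST) score from baseline to the end of treatment". The score is the sum of the longest forward and backward spans. "The DST will be conducted at baseline, 4 weeks, 8 weeks, and within 2 weeks of the end of treatment".
- **Secondary outcomes, SNSB-II.** Of the battery's five domains, "The attention domain includes the DST". On timing, "The SNSB-II will be assessed at screening and within 3 weeks of the end of treatment".
- **Assessment of eligibility.** Patients who pass the first screening step go on to a second, in which the investigators "assess cognitive function using the Seoul Neuropsychological Screening Battery-II (SNSB-II), on a separate day".
- **Secondary outcomes, MoCA-K.** The listed components include "short-term memory recall task, DST, serial 7 s". This test is also given at screening and after treatment.
- **Statistical analysis.** Post-test scores are analysed by ANCOVA, "using each group as the fixed factor and baseline score with strata factors (such as sex and age) as the covariate".

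The SNSB-II is a secondary outcome as a whole battery. The article gives the screening digit span no role in the DST analysis.

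**The concern.** A digit span score from a single occasion is a short, coarse measure, so one baseline score is a noisy covariate. The SNSB-II at screening supplies another score from the same test before randomisation, at no extra burden to patients. In a trial planned on 44 evaluable patients, a second pre-treatment score can narrow the confidence interval for the primary comparison. As the analysis is described, that information is collected and left unused.

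What is at stake is precision only. The treatment estimate is not biased, and the 5% error rate of the primary test is not affected.

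**Working it through.** **1. The plan's own figure.** Inputs from Sample size calculation and Statistical analysis: difference 0.87, SD 0.89, two-sided 5%, power 90%, equal arms.

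n per arm = 2 × (1.960 + 1.282)² × (0.89/0.87)² = 21.99, so 22 per arm and 44 in total. With 10% dropout, 22/0.9 = 24.4, so 25 per arm and 50 in total. Both stated figures reproduce. (By the noncentral t distribution, power at 22 per arm is 88.6%, and 23 per arm are needed for 90%. This does not bear on the present point.)

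**2. Scores available before treatment.** The SNSB-II at screening gives one digit span and the stand-alone DST at baseline gives another. These are two separately scheduled occasions. The digit item in the MoCA-K is left out of the count.

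**3. Gain when all occasions correlate equally.** Let r be the correlation between any two DST occasions within arm. The documents give no value; 0.5 to 0.8 is assumed. One covariate leaves a fraction 1 − r² of the variance. Two covariates leave 1 − 2r²/(1 + r). The ratio is (1 + 2r)/(1 + r)².

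| r | One score | Two scores | Ratio | 44/ratio |
|---|---|---|---|---|
| 0.5 | 0.750 | 0.667 | 0.889 | about 50 |
| 0.7 | 0.510 | 0.424 | 0.830 | 53 |
| 0.8 | 0.360 | 0.289 | 0.802 | about 55 |

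Residual variance falls by 11% to 20%. The confidence interval narrows by 1 − √0.889 = 6% to 1 − √0.802 = 10%.

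**4. Gain when screening correlates less with the outcome.** Let b be the baseline-to-end correlation, p screening-to-baseline and s screening-to-end. With both scores as separate covariates, the ratio is 1 − (s − bp)²/[(1 − b²)(1 − p²)].

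- b = p = 0.7, s = 0.6: 1 − (0.60 − 0.49)²/(0.51 × 0.51) = 0.953, a gain of about 5%.
- b = 0.7, p = 0.8, s = bp = 0.56: the numerator is zero, the ratio is 1, and nothing is gained.

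**5. Why not average the two scores.** In the last case the mean of the two scores has variance (1 + 0.8)/2 = 0.9 and covariance with the outcome (0.70 + 0.56)/2 = 0.63. It leaves 1 − 0.63²/0.9 = 0.559, against 0.51 with baseline alone. That is 10% more variance. Averaging can do harm, and it needs identical scoring in both settings, which the article does not state. A separate covariate needs neither condition.

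**6. Cost of a useless covariate.** Suppose baseline, sex and age take one parameter each. With group and intercept, 44 patients leave 39 residual degrees of freedom, or 38 with the extra covariate. For roughly normal covariates, the variance of the adjusted difference is inflated by about (N − 3)/(N − q − 3) with q covariates. Going from q = 3 to q = 4 multiplies it by 38/37 = 1.027, a cost of just under 3%. Net of this, the equal-correlation gain is 1 − 0.889 × 1.027 = 9% to 1 − 0.802 × 1.027 = 18%.

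**7. Effect on power.** Assume 0.89 is the SD of the change score. The single-baseline residual SD is then 0.89 × √((1 + r)/2), that is 0.771 to 0.844 for r = 0.5 to 0.8. Normal-approximation power at 22 per arm is 96% falling to 93%. With both scores and equal correlations it is 98% falling to 97%. The planned size is adequate either way for a difference of 0.87.

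**The case against.** The strongest case against is that nothing here is wrong. ANCOVA on one pre-specified baseline score is valid, the sample size reproduces, and power at the planned difference already exceeds 90% under the assumptions of step 7. The correlations are assumed, the largest gains need equal correlations, and under a plausible pattern of decay the gain is nil. An unseen analysis plan may also already deal with the covariates. All of this stands. It makes the point a suggestion and rules out averaging. It does not remove the case for a separate covariate, whose possible loss is small.

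A reader might also infer more than the documents support:

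- **That the DST is given twice after treatment, making six administrations.** The 2-week and 3-week windows overlap, and the article does not say whether the stand-alone DST and the SNSB-II digit span are one administration or two.
- **That the primary endpoint is open to choice.** The Primary outcome section fixes the test, time points, scoring rule and window.
- **That the DST is counted again as a secondary outcome.** It enters only as part of the SNSB-II, and also of the MoCA-K. It is not named as a secondary outcome itself, and whether the SNSB-II is analysed by total, domain or subtest may be fixed elsewhere. The article nowhere offers an SNSB-II attention result as confirmation.

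**Conclusion.** A cheap improvement, not an error. The stated analysis leaves a scheduled pre-treatment DST score unused. As a separate covariate it would lower the residual variance of the primary ANCOVA by 11% to 20% if DST occasions correlate equally at 0.5 to 0.8, or about 9% to 18% net of the lost degree of freedom. The gain falls to zero if the screening score adds nothing beyond baseline, and the loss is then just under 3%. These figures rest on correlations that the documents do not give.

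The single-baseline analysis remains valid, and 44 (50 with dropout) needs no change. On interpretation, only a caution is justified: an SNSB-II digit span result overlaps with the primary outcome, whether it comes from a shared or a second administration, and should not be read as independent evidence.

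**What to change.** Before unblinding, state in the protocol or analysis plan that the ANCOVA of the end-of-treatment DST includes group, the stand-alone baseline DST, the strata factors and, as an additional separate covariate, the digit span score from the screening SNSB-II. If the SNSB-II records forward and backward spans separately, enter their sum so that only one parameter is used. Do not average it with the baseline DST. Keep the stand-alone DST as the primary outcome, and put the screening score in the multiple imputation model as well. Add one sentence that any SNSB-II digit span result after treatment overlaps with the primary outcome.

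The cost is wording and one degree of freedom. The value is already scheduled for every patient who reaches the second screening step, and neither the visits nor the sample size change.

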### Sample size calculation

To assess the efficacy of the intervention, the minimal clinically important difference (MCID) of DST was considered. However, there was no well-established prior study to derive the MCID of DST. Thus, the effect size was calculated from a similar study examining acupuncture treatment for MCI.

The sample size is estimated based on the result from a previous study [29]. The mean difference in the DST score is assumed to be 0.87 and the standard deviation (SD) of that is assumed to be 0.89 between the acupuncture group and sham acupuncture group. Sample size calculation shows that a total of 44 patients is needed for 90% statistical power and 5% significance level. With an estimated dropout ratio of 10%, the necessary sample size is 50 patients (25 patients for each acupuncture group).

